### Data management

All data forms will be uploaded to the Microsoft Teams environment, password protected, and backed up in the Queen’s University cloud storage. The RA will enter all data in SPSS [68]. Data will be kept for seven to 10 years after. Data will be held in a secure environment on Canadian servers in the Queen’s University research data repository for faculty, students, and staff [65].

### Confidentiality

All information collected about potential participants will be destroyed should eligibility not be met for the study. All data collected from participants will be identified by a study identifier only to maintain participant confidentiality. No identifying information will be included when results of the study are shared. Participants will be asked to maintain confidentiality of other participants such as identifying information and meditation reflections. No record of the Zoom meetings will exist.

### Auditing trial conduct

This trial will be audited by the second author for completeness and accuracy of data collection and retention of participants across arms of this study.

### Ethics and dissemination

This trial has been approved by the Queen’s University Health Sciences & Affiliated Teaching Hospitals Research Ethics Board (approval number REH-768-20). This clinical trial has been registered at ClinicalTrials.gov for accessibility by other researchers. This research study received the written support of the Prince Edward Family Health Team and the Queen’s Family Health Team. The PI will inform the PhD committee of any changes to the protocol such as recruitment procedures, intervention, or data collection and analyses. As appropriate, amendments will be requested of Queen’s University HSREB and approvals received prior to any changes to this protocol. Protocol amendments will be communicated via ClinicalTrials.gov (ID NCT04415528) updates. Results will be disseminated through peer reviewed journals, international conferences, and primary care grand rounds.

### Consent

Prior to screening for eligibility, each potential participant will receive an emailed copy of the Letter of Information/Informed Consent and will provide informed consent to the PI at the beginning of the screening call (Additional file 1). Data gathered from screened potential participants not eligible to participate will be destroyed. The reason for ineligibility will be noted. All data will be anonymized. In the event of withdrawal from the study, the participant will have the choice of requesting that collected data be destroyed or to give consent to include data for analysis.

The purpose of this protocol is to ensure transparency and reproducibility of the results of this study. Therefore, this protocol will be available publicly through journals and trial registries [66, 71]. The deidentified data will be archived to Queen’s University Scholars Portal Dataverse, a repository for research data that is stored on Canadian servers in a secure environment, within 3 years of collection and will be available for sharing [72].

## Discussion

A potential limitation to this trial is that it is not powered to examine effectiveness and findings will not be generalizable to other populations. However, findings will inform planning of a definitive RCT including anticipated time required for recruitment, strategies to promote adherence, and sample size calculations. This study will not examine hypothesis testing based on the CONSORT extension. Due to COVID-19, this group has been modified for delivery in an online format to ensure the participants’ safety. This trial will provide unique information to international researchers and clinicians regarding a novel treatment for late-life anxiety and will become the first RCT to determine the feasibility of EFMT for older adults with late-life anxiety.

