**Discussion:**

The results of this trial will determine the feasibility and potential effectiveness of video-delivered EFMT for late-life anxiety compared to no treatment. If the results are promising, a larger randomized controlled trial may be conducted.

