### Sample size justification

A sample size of 48 participants will allow for intervention group sizes of six participants and wait listed control group sizes of six participants. There will be four blocks of participants, with 12 participants in each block, and groups of six participants. This will result in 24 participants per arm. Small sample sizes of 10–20 participants or more are appropriate for pilot testing of adherence to interventions and this study will exceed those numbers, thereby allowing for attrition [48, 49]. There are also pragmatic considerations to selecting the sample size for this study [50], which include planning to complete the study within a year with limited funding. The study will not be powered to detect significant changes on the secondary outcomes. As COVID-19 protocols prohibit groups meeting in person, this study has moved to Zoom, an online privacy protected platform [51]. Other COVID-19 adjustments pivots required will be shorter meetings of 1.5 h to avoid Zoom fatigue and smaller group sizes [40]. This will be sufficient to meet the study’s primary objectives of recruitment, retention, and completion rates to determine whether a large study is warranted.

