### Randomization

Random allocation will be conducted by the second author, immediately after each set of 12 participants has been enrolled into the study by the PI*.* Groups will begin on a rolling basis each time a block of 12 participants has been enrolled. To ensure a 1:1 random allocation between the intervention and control groups, the participants will be randomly assigned using the random allocation function in Excel.

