### Statistical methods

Data entry will be conducted by the RA. Data analysis will be conducted by the PI at the end of the study using SPSS V27 [68]. All data will be examined by running frequencies on each variable to determine if values are missing or out of range. Possible errors will be compared to raw data and corrected as necessary to ensure accuracy [67]. As is recommended for pilot feasibility studies, the following descriptive statistics will be used: for continuous variables, minimum, maximum, mean, median, mode standard deviation, skewness, and kurtosis; if continuous variables are skewed, non-parametric descriptive statistics will be reported; for categorical variables, frequencies will be used [69, 70]. Graphical displays such as histograms or boxplots will be presented to demonstrate and better understand the central tendency and dispersion of the data [67]. Recruitment, enrollment, and retention rates will be calculated. Rates of attendance and adherence to each component of the intervention will also be calculated to determine acceptability.

To examine whether there have been potential changes in the secondary outcomes, descriptive statistics will be used to analyze and present demographic and baseline data. Categorical and ordinal data will be compared using chi-square. Continuous data will be compared using a *t*-test. The mean change in the intervention group and wait list control group outcomes will be compared post intervention (T3) using an independent samples *t*-test, and Cohen’s *d* will be calculated for effect size [67]. Data from each of the groups will be combined to form a larger sample size to evaluate the effect of the intervention. Analysis of pooled data will be conducted using a paired sample *t*-test and Cohen’s *d* to examine the intervention effect over baseline measures. Change over time for the intervention group from T1 to T2 to T3 will be calculated by using repeated measures ANOVA to determine if change has occurred and/or is maintained in the intervention group.

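### The protocol disclaims hypothesis testing, but its Statistical methods section plans t-tests, chi-square tests and a repeated measures ANOVA; the two must be reconciled

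*Protocol article*

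**What the plan says.** Two places in the Protocol article set a non-inferential stance. The Discussion says "This study will not examine hypothesis testing based on the CONSORT extension". The Sample size justification says "The study will not be powered to detect significant changes on the secondary outcomes".

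The first paragraph of Statistical methods is in keeping with this: it presents descriptive statistics as the recommended approach for pilot feasibility studies and, for the primary outcomes, says "Recruitment, enrollment, and retention rates will be calculated".

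The second paragraph of the same section goes further. Directly after a sentence on describing demographic and baseline data it says "Categorical and ordinal data will be compared using chi-square", and adds a t-test for continuous data. It then plans:
- an independent-samples t-test of mean change between the arms, placed at T3, with Cohen's d;
- a paired t-test on the pooled arms, with Cohen's d;
- a repeated measures ANOVA over T1, T2 and T3 in the intervention arm, whose stated purpose is to decide whether change occurred and whether it lasted.

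The abstract's Discussion paragraph says that the results "will determine the feasibility and potential effectiveness of video-delivered EFMT for late-life anxiety compared to no treatment".

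**The concern.** A trial cannot both abstain from hypothesis testing and run this set of tests. Whoever analyses the data has to break one statement or the other, and a reader of the results will not know whether a p-value was meant to carry weight.

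What is at stake is how the secondary results are read. With an unpowered test, a non-significant result is easily taken as no effect and a chance significant one as promise. The abstract links promising results to a possible larger trial, so either misreading could colour that decision. If the chi-square and t-tests do compare the arms at baseline, they test differences that randomisation has already made a matter of chance, and their results answer no useful question.

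**Working it through.** **1. The plan's own figures.** The sample size section says "There will be four blocks of participants, with 12 participants in each block, and groups of six participants" and "This will result in 24 participants per arm". The arithmetic holds: 4 × 12 = 48, 48 / 2 = 24 per arm, and 16 per month × 3 months = 48. The article gives no alpha, effect size, standard deviation or power, so there is no power figure to reproduce.

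**2. The passages side by side.**
- Discussion: no hypothesis testing.
- Sample size justification: no power for the secondary outcomes.
- Statistical methods, second paragraph: three inferential analyses of the secondary outcomes, one of them with an explicit yes/no purpose, plus chi-square and t-tests.
- No section calls any of these exploratory or says that their p-values will be set aside.

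**3. Whether the chi-square and t-tests are baseline tests.** The two sentences name neither arms nor a time point, and their paragraph opens with changes in the secondary outcomes. They do follow directly on the sentence about demographic and baseline data, and the design allocates at random ("To ensure a 1:1 random allocation between the intervention and control groups"). Baseline comparison of the arms is therefore the most natural reading, but it is an inference.

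**4. What a between-arm test could show.** Assumptions: two-sided alpha 0.05, a true standardised difference d = 0.5 (illustrative), and one arm treated, the other not.
- Noncentrality = d × √(n/2), with 2n − 2 degrees of freedom.
- n = 24 per arm: 0.5 × √12 = 1.73 on 46 df, power 0.396, about 40%.
- At the 65% retention threshold, 0.65 × 24 = 15.6, rounded to 16 per arm: 0.5 × √8 = 1.41 on 30 df, power 0.278, about 28%.

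**5. Precision of an observed d = 0.5 with 16 per arm.**
- SE(d) = √(2/n + d²/(4n)) = √(2/16 + 0.25/64) = √0.1289 = 0.359.
- 95% CI = 0.5 ± 1.96 × 0.359 = 0.5 ± 0.70, that is -0.20 to 1.20.

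The interval runs from a small difference in the wrong direction to a very large benefit. Reporting it is honest about what the trial can show; a p-value from the same data hides it.

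**6. Where the between-arm contrast sits.** The secondary objectives compare people who receive the intervention with people who do not. The section on T3 data collection places T3 after the wait-list arm has completed its own programme, so at T3 both arms have been treated. The figures in steps 4 and 5 describe a treated-versus-untreated comparison, which exists at T2 but not at T3.

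**7. Feasibility rates, for completeness.** The smallest count that meets the 65% retention rule is 32 of 48 (66.7%). The Wilson interval is (p + z²/2n ± z√(p(1−p)/n + z²/4n²)) / (1 + z²/n). With p = 0.6667, n = 48 and z = 1.96 this is (0.7067 ± 0.1392) / 1.0800, or 53% to 78%.

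**The case against.** The strongest reply is that the Discussion sentence, read with its neighbours on lack of power, means only that no confirmatory testing is intended. The secondary aims are hedged throughout as potential changes, no alpha or significance rule is stated, both named t-tests are paired with Cohen's d, and tests in pilot trials are common. Part of this stands: the authors plainly do not claim a powered comparison, and a single sentence labelling the analyses exploratory would remove the literal conflict. But the article contains no such sentence. It says that testing will not be examined and then gives an ANOVA a yes/no purpose.

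A reader might infer more than the document supports:
- **That the feasibility rates are wrongly planned because no interval is named.** Interval reporting is detail that a condensed article can leave to a fuller plan. Calculating rates is not an error.
- **That a family-wise false-positive rate can be quoted for three scales and three analyses.** No alpha is given, the analyses reuse the same participants' changes, and the scales come from the same people, so independence fails. Two of the three analyses are also uncontrolled within-person comparisons, where natural course or regression to the mean could produce change without any treatment effect.
- **That the definitive trial will be mis-sized from the observed d.** The Discussion says only that findings will inform sample size calculations. It does not say that d will be the target difference; the standard deviation and retention are equally consistent inputs.

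**Conclusion.** The point holds as a contradiction between the Discussion and the Statistical methods section, supported by the sample size section's own disclaimer of power. A separate analysis plan could not remove it, because both statements stand in this article.

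The effect is confined to how the secondary outcomes are analysed and read. The power and interval figures rest on an assumed alpha, an illustrative d, and, for 16 per arm, retention at about the 65% threshold; they apply to a T2 contrast. The remark on baseline tests depends on the natural but unstated reading of two sentences. The sample size of 48 and the feasibility criteria are not called into question here. The plan should be changed, and the change is small.

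**What to change.** Rewrite the second paragraph of Statistical methods so that it agrees with the Discussion:
- Present demographic and baseline data descriptively by arm, with no chi-square or t-tests.
- Report each secondary contrast as a mean difference and a standardised difference, each with a 95% confidence interval, in place of a significance test.
- Place the between-arm contrast at T2, when the wait-list arm is still untreated. Data at T2 are already planned.
- Report the pooled pre-post change and the intervention arm's course over T1 to T3 as mean changes with 95% confidence intervals, described as uncontrolled.

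Deleting the Discussion sentence and labelling the tests exploratory would also end the contradiction, but it fits the trial's stated stance less well and would leave the T3 placement as it is.

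A useful addition, though not a correction, is to show each feasibility rate with its 95% confidence interval beside the threshold.

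The cost is wording and standard software output, with no new data or participants. The only downside is that the conclusions become more cautious.

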## Conclusion

Significant rates of anxiety among older adults can be expected to increase as the world population ages and within the COVID-19 and post COVID-19 environment [24, 73, 74]. Anxiety is a leading cause of disability in older adults [75]. EFMT is a low-cost non-pharmacological treatment that could be offered in primary care and community settings. EFMT has the potential to provide older adults with the knowledge, skills, and practice to reduce anxiety.

## Data Availability

Data will be kept for 7 to 10 years after it is analyzed and published. Data will be held in a secure environment on Canadian servers in the Queen’s University Dataverse, a research data repository for faculty, students and staff [65].
